##### 7.3.1.B Severity or Grading of Adverse Events

The severity of all AEs and/or ARs (serious and non-serious) in this trial should be graded using the toxicity gradings in [Section 18.3 – Appendix 2](#) (DIVISION OF AIDS TABLE FOR GRADING THE SEVERITY OF ADULT AND PEDIATRIC ADVERSE EVENTS).

##### 7.3.1.C Causality

The investigator must assess the causality of all serious events or reactions in relation to the trial therapy using the definitions in [Table 7.2: Assigning Type of SAE Through Causality](#). There are five categories: unrelated, unlikely, possible, probable, and definitely related. If the causality assessment is unrelated or unlikely to be related, the event is classified as an SAE. If the causality is assessed as possible, probable or definitely related, then the event is classified as an SAR.

**Table 7.2: Assigning Type of SAE Through Causality**

| RELATIONSHIP | DESCRIPTION                                                                                                                                                                                                                                                                                                               | SAE TYPE      |
|--------------|---------------------------------------------------------------------------------------------------------------------------------------------------------------------------------------------------------------------------------------------------------------------------------------------------------------------------|---------------|
| Unrelated    | There is no evidence of any causal relationship                                                                                                                                                                                                                                                                           | Unrelated SAE |
| Unlikely     | There is little evidence to suggest that there is a causal relationship (for example, the event did not occur within a reasonable time after administration of the trial medication). There is another reasonable explanation for the event (for example, the patient's clinical condition, other concomitant treatment). | Unrelated SAE |

|            |                                                                                                                                                                                                                                                                                                                                 |     |
|------------|---------------------------------------------------------------------------------------------------------------------------------------------------------------------------------------------------------------------------------------------------------------------------------------------------------------------------------|-----|
| Possible   | There is some evidence to suggest a causal relationship (for example, because the event occurs within a reasonable time after administration of the trial medication). However, the influence of other factors may have contributed to the event (for example, the patient's clinical condition, other concomitant treatments). | SAR |
| Probable   | There is evidence to suggest a causal relationship and the influence of other factors is unlikely.                                                                                                                                                                                                                              | SAR |
| Definitely | There is clear evidence to suggest a causal relationship and other possible contributing factors can be ruled out.                                                                                                                                                                                                              | SAR |

If an SAE is considered to be related to trial treatment and drug is stopped or the dose modified, refer to [Section 5.2.4 - Dose Modifications, Interruptions & Discontinuations](#).

#### 7.3.1.D Expectedness

If there is at least a possible involvement of the trial treatment (or comparator), the investigator must assess the expectedness of the event. An unexpected adverse reaction is one not previously reported in the current Summary of Product Characteristics (SPC) or one that is more frequent or more severe than previously reported. The definition of an unexpected adverse reaction (UAR) is given in [Table 7.1: Definitions](#). Please refer to latest SPC for L-AmB for a list of expected toxicities associated with the drugs being used in this trial. If a SAR is assessed as being unexpected, it becomes a SUSAR.

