### 5.2.4 DOSE MODIFICATIONS, INTERRUPTIONS & DISCONTINUATIONS

See manufacturer's latest Summary of Product Characteristics (SPC) for L-AmB, Amphotericin, Flucytosine, and Fluconazole for dose adjustments in renal/hepatic insufficiency and management of expected adverse events. The Ambition trial treatment document may also be referenced in the absence of an internet connection.

- <http://www.medicines.org.uk/emc/medicine/1236>
- <http://www.medicines.org.uk/emc/medicine/559>
- <https://www.drugs.com/pro/flucytosine.html>
- [http://www.cipla.co.za/wp-content/uploads/2013/10/sep\\_cipla-fluconazole-50mg.pdf](http://www.cipla.co.za/wp-content/uploads/2013/10/sep_cipla-fluconazole-50mg.pdf)

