| Unexpected Adverse Reaction (UAR)                                                                                      | An adverse reaction, the nature or severity of which is not consistent with the information about the medicinal product in question set out in the Summary of Product Characteristics (SPC) or Investigator Brochure (IB) for that product.                                                                                                                                                                                                                            |
| Serious Adverse Event (SAE) or Serious Adverse Reaction (SAR) or Suspected Unexpected Serious Adverse Reaction (SUSAR) | Respectively any adverse event, adverse reaction or unexpected adverse reaction that: 
 
▪ Results in death
 
▪ Is life-threatening*
 
▪ Requires hospitalisation or prolongation of existing hospitalisation**
 
▪ Results in persistent or significant disability or incapacity
 
▪ Consists of a congenital anomaly or birth defect
 
▪ Is another important medical condition***
 
 |

\*The term life-threatening in the definition of a serious event refers to an event in which the patient is at risk of death at the time of the event; it does not refer to an event that hypothetically might cause death if it were more severe, for example, a silent myocardial infarction.

\*\*Hospitalisation is defined as an inpatient admission, regardless of length of stay, even if the hospitalisation is a precautionary measure for continued observation. Hospitalisations for a pre-existing condition, that has not worsened or for an elective procedure do not constitute an SAE.

\*\*\* Medical judgement should be exercised in deciding whether an AE or AR is serious in other situations. The following should also be considered serious: important AEs or ARs that are not immediately life-threatening or do not result in death or hospitalisation but may jeopardise the subject or may require intervention to prevent one of the other outcomes listed in the definition above; for example, a secondary malignancy, an allergic bronchospasm requiring intensive emergency treatment, seizures or blood dyscrasias that do not result in hospitalisation or development of drug dependency. Presence of malaria is not an SAE unless the current infection is life threatening.

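### Section 7.3.1.D names only the L-AmB SPC as the list of expected toxicities, in conflict with the product-specific definition in Table 7.1 to which it refers

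*Protocol*

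**What the plan says.** Section 7.3.1.D sets the scope of the assessment: "If there is at least a possible involvement of the trial treatment (or comparator), the investigator must assess the expectedness of the event". The comparator is therefore included.

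The section restates the meaning of an unexpected reaction in general terms, by reference to the current SPC without naming a product. It counts a reaction as unexpected if it is absent from that document, or is more frequent or more severe than reported there. It also cross-refers to Table 7.1 ("The definition of an unexpected adverse reaction (UAR) is given in" that table). It then gives the practical instruction: "Please refer to latest SPC for L-AmB for a list of expected toxicities associated with the drugs being used in this trial". The consequence follows at once: "If a SAR is assessed as being unexpected, it becomes a SUSAR".

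Table 7.1 judges the nature or severity of the reaction against the "information about the medicinal product in question set out in the Summary of Product Characteristics (SPC) or Investigator Brochure (IB) for that product".

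Section 5.2.4 cites four reference documents, the "Summary of Product Characteristics (SPC) for L-AmB, Amphotericin, Flucytosine, and Fluconazole for dose adjustments", and in the same sentence extends the reference to the management of expected adverse events.

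**The concern.** The general definition and the working instruction point to different documents. Table 7.1 asks whether the reaction is known for the drug under suspicion. The instruction gives the investigator the list for one drug, L-AmB, and presents it as covering the drugs used in the trial. Control patients never receive L-AmB, so for a suspected deoxycholate reaction the named list belongs to another product.

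What is at stake is the classification of serious reactions. If the sentence is taken literally, two errors are possible:

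- A reaction listed for the suspected drug but not for L-AmB would be called unexpected, giving a false SUSAR.
- A reaction listed for L-AmB but not for the suspected drug would be called expected, and a true SUSAR would be missed.

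The second error matters more, because an expedited report could then be lost.

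**Working it through.** No arithmetic applies beyond a count. The check is a comparison of the relevant sections.

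| Question | Section | What it gives |
|---|---|---|
| Which drugs are used? | 5.2.1 | Test arm: L-AmB, fluconazole, flucytosine. Control arm: amphotericin B deoxycholate, flucytosine, fluconazole |
| Whose reactions need an expectedness judgement? | 7.3.1.D | The trial treatment or the comparator |
| Which products are named as such? | 7.1.1 | L-AmB as IMP, amphotericin B as comparator |
| Against which document, by definition? | Table 7.1 | The SPC or IB of the product concerned |
| Against which document, by instruction? | 7.3.1.D | The L-AmB SPC |
| Which SPCs does the protocol cite? | 5.2.4 | L-AmB, amphotericin, flucytosine, fluconazole |

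**Count.** Four antifungals are used and four SPCs are cited in 5.2.4, but one SPC is named for expectedness. The control arm has three antifungals, and none is the product whose SPC is named.

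**Which drugs are affected.** The narrowest reading takes 7.1.1 as the limit, so that only L-AmB and amphotericin B are assessed. The comparator is still sent to another product's SPC, so the conflict stands. On the wider reading, where the wording about the drugs used in the trial includes the partner drugs, flucytosine and fluconazole are affected too, and they are given in both arms.

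**Which events are affected.** SUSAR status arises only for events that are serious and judged possibly, probably or definitely related (7.3.1.C and 7.3.1.D). With 425 control patients planned (3.3), the exposed set is the serious, related reactions among them. It is not every amphotericin reaction. The protocol gives no rate for that set.

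**Consequence for reporting.** Section 7.4 puts fatal and life-threatening SAEs and SUSARs on a 7-day clock and other SUSARs on a 15-day clock. The 7-day wording can be read to cover fatal and life-threatening SAEs whether or not they are unexpected. On that reading the expectedness label makes no difference at 7 days. It clearly decides whether a 15-day report is made.

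**A second mismatch.** Section 7.3.1.D counts greater frequency as a ground for unexpectedness, whereas Table 7.1 uses nature or severity only. The two mismatches can compound. Section 1.1 describes less nephrotoxicity and anaemia and fewer infusion reactions with L-AmB than with deoxycholate. If a deoxycholate reaction were judged for frequency against an L-AmB list, a familiar toxicity could look more frequent than reported. This assumes that the list gives frequencies, which cannot be checked here.

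**The case against.** The strongest reply is that a reader of the whole section reaches the right rule. The sentence before the instruction sends the investigator to Table 7.1, the restated definition is generic, and nothing says that the L-AmB SPC is the only permitted source. Section 5.2.4 also links all four SPCs to expected adverse events. This stands in part. A reader might infer that the L-AmB SPC replaces Table 7.1 for all four drugs, but the protocol does not say so. What remains is that the one document named for the task does not match the definition, and section 7.3.2 tells site staff to complete the SAE form on the guidance given in these sections.

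The second reply is central review. Under 7.3.1 the chief investigators or a delegate evaluate every SAE for expectedness and identify which reported SUSARs qualify. Section 7.4 adds medical review of all SAE reports. Only the local causality opinion is protected from being overruled. This also stands: a wrong site label does not by itself trigger a report to authorities, and a missed SUSAR may be recovered. The safeguard is incomplete, because neither section names the reference document that the reviewers should use.

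The third reply is that no SPC is at hand, so no particular reaction can be shown to be misclassified, and any imbalance between arms is conjecture. That is correct, and the point is limited accordingly.

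**Conclusion.** The inconsistency is real and is a matter of wording as written. For amphotericin B deoxycholate it holds on any reading of scope. For flucytosine and fluconazole it depends on whether reactions to them are assessed for expectedness, which 7.1.1 leaves open.

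Misclassification in either direction is a risk if the sentence is followed literally and central review does not correct it. The number of affected reports cannot be derived, and the effect is clearest for SUSARs on the 15-day clock.

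A reader might go further and infer that every control-arm amphotericin reaction is judged wrongly, or that each mislabelled event leads to an expedited report. The documents do not support either: only serious related reactions can become SUSARs, and review comes before reporting.

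No trial result is touched. The primary endpoint is all-cause mortality, and the adverse event analyses in 9.2 and 9.5 use DAIDS grade III/IV, not SUSAR status. The point deserves correction because it concerns regulatory safety reporting and is cheap to put right.

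**What to change.** In section 7.3.1.D, replace the reference to the L-AmB SPC with the latest SPC (or IB) of the suspected product, and point to the four SPCs already cited in section 5.2.4. That brings the instruction into line with Table 7.1.

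Reconcile the criterion as well: either remove greater frequency from 7.3.1.D or add it to Table 7.1, so that one definition applies throughout.

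A rule for events with several suspected drugs, or a change to the product classification in 7.1.1, would be a separate decision for the sponsor and is not needed to correct this defect.

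The cost is one amended sentence, one aligned criterion, and a matching line in any SAE form guidance. The reference documents are already linked in the protocol, and neither the sample size nor the analyses change.

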#### 7.3.1.E Notification

The co-ordinating centre should be notified of all SAEs within 24 hours of the investigator becoming aware of the event.

Investigators should notify the co-ordinating centre of all SAEs occurring from the time of randomisation until 30 days after the last protocol treatment administration. SARs and SUSARs must be notified to the co-ordinating centre until trial closure.

### 7.3.2 NOTIFICATION PROCEDURE

1. The SAE eCRF must be completed by the investigator (the consultant named on the Signature List and Delegation of Responsibilities Log who is responsible for the patient's care), with due care being paid to the grading, causality and expectedness of the event as outlined above. In the absence of the responsible investigator, the form should be completed by a member of the site trial team. The responsible investigator should subsequently check the SAE eCRF and make changes as appropriate. The initial report must be followed by detailed, follow-up and final reports as appropriate.

The minimum criteria required for reporting an SAE are the trial number and date of birth, name of investigator reporting and why the event is considered serious.

2. The SAE eCRF must be completed on the trial database. Once submitted, the co-ordinating centre is alerted of the submission by an automated email to its dedicated pharmacovigilance email address: [[contact]](mailto:[contact]).
3. Follow-up: patients must be followed up until clinical recovery is complete and laboratory results have returned to normal or baseline, or until the event has stabilised. Follow-up should continue after completion of protocol treatment if necessary. A further SAE eCRF,

indicated as 'Follow-up' should be completed as information becomes available. Extra, annotated information and/or copies of test results may be provided separately. The patient must be identified by trial number, date of birth and initials only. The patient's name should not be used on any correspondence and should be deleted from any test results.

4. Staff should follow their institution's procedure for local notification requirements.

## **7.4 SPONSOR RESPONSIBILITIES**

The co-ordinating centre is undertaking a number of duties as delegated by the trial sponsor and is responsible for the reporting of SAEs, SUSARs, and other SARs to the regulatory authorities (competent authorities of countries in which the trial is taking place) and the research ethics committees, as appropriate. Medically-qualified staff at the co-ordinating centre and/or the Chief Investigator (or a medically-qualified delegate) will review all SAE reports received. The causality assessment given by the local investigator at the hospital cannot be overruled; in the case of disagreement, both opinions will be provided in any subsequent reports.

Fatal and life-threatening SAEs and SUSARs must be reported to the competent authorities within 7 days of the co-ordinating centre becoming aware of the event; other SUSARs must be reported within 15 days.

The co-ordinating centre will also keep all investigators informed of any safety issues that arise during the course of the trial.

The co-ordinating centre, as delegated by the Sponsor, will submit Annual Safety Reports in the required format to Competent Authorities (Regulatory Authority and Ethics Committee).

Drug companies involved will be notified of reportable events as appropriate. The co-ordinating centre will also provide companies with a copy of the Annual Safety Report in the required format.

## QUALITY ASSURANCE & CONTROL

### 8.1 RISK ASSESSMENT

The Quality Assurance (QA) and Quality Control (QC) considerations have been based on a formal Risk Assessment, which acknowledges the risks associated with the conduct of the trial and how to address them with QA and QC processes. QA includes all the planned and systematic actions established to ensure the trial is performed and data generated, documented and/or recorded and reported in compliance with the principles of ICH GCP and applicable regulatory requirements. QC includes the operational techniques and activities done within the QA system to verify that the requirements for quality of the trial-related activities are fulfilled. This Risk Assessment has been reviewed by the Sponsor and has led to the development of a Monitoring Plan, standard operating procedures and a tailored training schedule for all parties involved in the trial.

### 8.2 CENTRAL MONITORING AT THE CO-ORDINATING CENTRE

Co-ordinating centre staff will review electronic Case Report Form (eCRF) data for errors and missing data points.

Other essential trial issues, events and outputs will be detailed in the Monitoring and Quality Management Plan that is based on the trial-specific Risk Assessment.

### 8.3 ON-SITE MONITORING

The frequency, type and intensity for routine monitoring and the requirements for triggered monitoring will be detailed in the Monitoring Plan. This plan will also detail the procedures for review and sign-off. The study may be subject to audit by the London School of Hygiene & Tropical Medicine under their remit as sponsor, the Study Coordination Centre and other regulatory bodies to ensure adherence to GCP.

#### 8.3.1 DIRECT ACCESS TO PATIENT RECORDS

Participating investigators should agree to allow trial-related monitoring, including audits, ethics committee review and regulatory inspections by providing direct access to source data and documents as required. Patients' consent for this must be obtained.

#### 8.3.2 CONFIDENTIALITY

We plan to follow the principles of the UK Data Protection Act (DPA) regardless of the countries where the trial is being conducted. Consent forms will be stored under the supervision of each local PI in a secured office and accessible to trial staff only. The database does not hold personal details as participants are identified by their study number throughout the trial.

## STATISTICAL CONSIDERATIONS

### 9.1 METHOD OF RANDOMISATION

Patients will be randomised individually and randomisation codes will be generated using SAS PROC PLAN via permuted-block randomisation method stratified by site. Block sizes will vary at 4 and 6. Randomisation lists will be created for each site by an independent statistician and each list will be housed on the electronic database system (EDC) for that particular site, and will be inaccessible to trial staff except to randomise the next eligible participant. Randomised allocation for each trial participant will be provided to trial staff by extracting the next available randomisation allocation, obtained from the randomisation list for that site housed on the database. Internally the EDC selects against an electronic randomization list prepared in advance by the Statistician. The EDC guarantees to make the selection in the natural order of the list filtering by study site only. Once a selection is made, the randomization record is tagged with the patient study allocated identifier, date and time of randomization and other EDC system audit values (username, machine name, etc). A tagged record cannot be selected more than once.

It is impractical to blind the study because of the very high doses of short course L-AmB (currently up to 20 drug vials per dose depending on patient weight) used in the intervention arm, compared to the standard amphotericin B deoxycholate (often only a single vial per patient), given daily, in the control arm. Bias will be minimised by the use of an objective clinical endpoint “all-cause 10-week mortality” as the primary outcome. Laboratory technicians performing EFA will be blinded to study arm. The trial statistician will be blinded regarding the treatment code when developing the statistical analysis plan and writing the statistical analysis programmes, which will be validated and completed using dummy randomisation codes.

